# Hysteropexy in the treatment of uterine prolapse stage 2 or higher: a multicenter randomized controlled non-inferiority trial comparing laparoscopic sacrohysteropexy with vaginal sacrospinous hysteropexy (LAVA-trial, study protocol)

**DOI:** 10.1186/1472-6874-14-112

**Published:** 2014-09-17

**Keywords:** Pelvic organ prolapse, Uterine descent, Hysteropexy, Vaginal sacrospinous hysteropexy, Laparoscopic sacrohysteropexy

## Abstract

**Background:**

Pelvic organ prolapse is a common health problem: the lifetime risk of undergoing surgery for pelvic organ prolapse by the age of 85 years is 19%. Pelvic organ prolapse has significant negative effects on a woman’s quality of life. Worldwide, vaginal hysterectomy is the leading treatment method for patients with symptomatic uterovaginal prolapse. Several studies have shown that vaginal sacrospinous hysteropexy and laparoscopic sacrohysteropexy are safe and effective alternatives in treating uterine descent. To date, it is unclear which of these techniques leads to the best operative result and the highest patient satisfaction. Therefore, we conducted the LAVA trial.

**Methods:**

The LAVA trial is a randomized controlled multicenter non-inferiority trial. The study compares laparoscopic sacrohysteropexy with vaginal sacrospinous hysteropexy in women with uterine prolapse stage 2 or higher. The primary outcome of this study is surgical success of the apical compartment at 1 and 5 years follow-up. Secondary outcomes are subjective improvement on urogenital symptoms and quality of life (assessed by disease-specific and general quality of life questionnaires), complications following surgery, hospital stay, post-operative recovery, sexual functioning and costs-effectiveness. Evaluation will take place pre-operatively, and 6 weeks, 6 months, 12 months and annually till 60 months after surgery. Validated questionnaires will be used.

Analysis will be performed according to the intention to treat principle. Based on comparable recurrence rates of 3% and a non-inferiority margin of 10%, 62 patients are needed in each arm to prove the hypothesis with a 95% confidence interval.

**Discussion:**

The LAVA trial is a randomized controlled multicenter non-inferiority trial that will provide evidence whether the efficacy of laparoscopic sacrohysteropexy is non-inferior to vaginal sacrospinous hysteropexy in women with symptomatic uterine prolapse stage 2 or higher.

**Trial registration:**

Netherlands Trial Register (NTR): NTR4029

## Background

Pelvic organ prolapse (POP) is defined as the descent of one or more of the pelvic organs. POP is a common health problem. As life expectancy increases, a significantly greater number of women will present with POP requiring surgery. Given a life expectancy of 85 years, the lifetime risk of women undergoing a surgery for POP is 19% [1]. POP has significant negative effects on a woman’s quality of life, ranging from physical discomfort, psychological and sexual complaints to occupational and social limitations.

The etiology of POP is multifactorial: vaginal childbirth, advancing age and increasing body-mass index are the most consistent risk factors [2, 3].

Women can present with prolapse of one or more compartments. Symptoms are commonly attributed to the anatomical compartments that are involved. Anterior vaginal wall prolapse concerns the urethra and/or the bladder (uretrocele, cystocele). Apical prolapse entails either the uterus or vaginal cuff after hysterectomy. Posterior vaginal wall prolapse involves the rectum (rectocele) but can also include the small intestines (enterocele). This study will focus on the treatment of uterine prolapse.

Worldwide, vaginal hysterectomy is the most frequently used treatment method for patients with symptomatic uterovaginal prolapse: it appeared to be the procedure of choice in the United Kingdom (82%) [4] and in Australia and New Zealand (79%) [5]. Although the literature is inconclusive, it has been suggested that hysterectomy may cause nerve supply damage and disrupt supportive structures of the pelvic floor, subsequently increasing the risk of future vaginal vault prolapse [6]. Furthermore, hysterectomy alone fails to address the underlying deficiencies in pelvic support causing uterine prolapse. Up to 11.6% of women undergoing hysterectomy subsequently present with vaginal vault prolapse [7] and the frequency of posthysterectomy vault prolapse requiring surgical repair is estimated between 6 and 8% [8].

Many other techniques for the treatment of uterine descent have been described, including vaginal, abdominal and laparoscopic procedures.

One procedure for uterine descent with uterine preservation is vaginal sacrospinous hysteropexy. In this procedure, the uterus is suspended to the sacrospinous ligaments with permanent sutures. In several studies, this technique was demonstrated to be a safe procedure for the primary treatment of uterine descent [9–11]. In a prospective observational study of 72 women with uterine descent, sacrospinous hysteropexy significantly reduced all urogenital and several defecatory symptoms and significantly improved quality of life. It also cured the uterine descent in 93.1% of women [12]. The procedure is associated with a few serious complications. The most common complication is buttock pain on the side where the sacrospinous sutures have been passed, this occurs in approximately 10-15% of the women, but resolves typically in days to months. One prospective study and one retrospective study comparing vaginal hysterectomy to vaginal sacrospinous hysteropexy demonstrated no significant difference in anatomical outcome, while hospital stay was shorter, less pain was experienced and recovery was quicker in the latter group [13–15]. These studies conclude that vaginal sacrospinous hysteropexy is associated with a faster complete recovery compared to vaginal hysterectomy. In both groups high recurrence rates of anterior vaginal wall prolapse were demonstrated (50% in hysterectomy group vs. 65% in sacrospinous hysteropexy group) [15]. It is believed that the change in axis of the vagina after a sacrospinous hysteropexy predisposes to an increased risk of prolapse of the anterior compartment [16].

Another procedure for uterine descent with uterine preservation is laparoscopic sacrohysteropexy. In this procedure, the uterus is elevated by attaching the cervix to the sacral promontory using a mesh. One prospective study suggests that sacrohysteropexy is a safe and effective procedure. One out of 13 women (7.7%) had a recurrence of uterine prolapse (mean follow-up 15.6 months) [17]. However, in this study the sacrohysteropexy was performed by laparotomy.

Another prospective study in which laparoscopic sacrohysteropexy was performed in 51 women showed no objective recurrence of uterine prolapse during a 10 weeks follow-up [18]. Laparoscopic sacrohysteropexy may have some complications. Typically, the use of a synthetic mesh implies a theoretical risk of erosion into an adjacent structure, or adhesion of bowel to the mesh, with subsequent development of symptoms and eventually signs of acute or chronic obstruction. Current experience anticipates a mesh related complication in less than 1% using a polypropylene mesh in abdominal correction of pelvic organ prolapse [19].

Based on literature, it seems that uterus suspension in case of uterine descent could be an effective procedure and avoid the limitations of hysterectomy. To our knowledge, a study comparing vaginal sacrospinous hysteropexy with laparoscopic sacrohysteropexy for the treatment of uterine descent has not been performed yet. It is unclear which of these treatment modalities results in the best anatomic correction and the highest patient satisfaction. Herein, we report on a multicenter randomized controlled trial to determine whether the efficacy of laparoscopic sacrohysteropexy is similar to vaginal sacrospinous hysteropexy in women with symptomatic uterine prolapse POP-Q stage 2 or higher.

## Methods/Design

### Study objectives

The objective of this study is to determine whether laparoscopic sacrohysteropexy in women with uterine descent stage 2 or higher improves outcome in terms of recurrence of prolapse, quality of life, complications, hospital stay, post-operative recovery, sexual functioning and costs-effectiveness compared to vaginal sacrospinous hysteropexy.

#### Hypothesis

Based on the literature, we hypothesize that there is no difference in surgical success rate of the apical compartment between laparoscopic sacrohysteropexy and vaginal sacrospinous hysteropexy in symptomatic women with uterine descent POP-Q stage 2 or higher. Possibly, laparoscopic sacrohysteropexy might be associated with quicker post-operative recovery, less dyspareunia post-operatively and lower recurrence rates with respect to the anterior vaginal wall.

### Study design

The LAVA-trial is a prospective, randomized controlled non-blinded clinical trial conducted with the aim to determine non-inferiority of the primary endpoint (surgical success of the apical compartment) between laparoscopic sacrohysteropexy and vaginal sacrospinous hysteropexy. The study will be an open label study, as it is impossible to blind the participating patients and the health care workers for the surgical procedure to which the woman is allocated. However, follow-up at six months, one and five years will be done by a physician not involved in the surgery. Post-operative follow-up will take place after 6 weeks, 6 months, 12 months and annually thereafter until 5 years. Patients will undergo a standard gynecological examination (including a POP-Q examination) and fill in questionnaires. The study design is presented in Figure 1.

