**Study design.**

### Primary and secondary outcomes

Surgical success of the middle compartment at 1 and 5 years follow-up in both study groups will be considered as the primary outcome. Success is defined as position of the cervix at or above the mid-vagina (C < -TVL/2), no symptoms (defined as no symptoms of vaginal bulging and protrusion on the validated questionnaire) and no reoperation or pessary use for recurrent apical prolapse [20]. Failure in one of these areas will constitute a failure. Secondary outcomes of this study include prolapse of the anterior and posterior compartment, subjective outcome and improvement in general and disease-specific quality of life, complications, hospital stay, postoperative recovery, sexual functioning, cost-effectiveness and uterine issues (e.g. abnormal bleeding, cervical dysplasia) and the need for subsequent hysterectomy.

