### Data collection

All patients will undergo routine gynecological examination, which is part of the standard procedure before surgery. This examination includes pelvic ultrasound to exclude uterine or ovarian disease, routine PAP-smear and vaginal inspection in 45° semi-upright position for staging uterovaginal prolapse by a POP-Q examination. Maximum prolapse is demonstrated and identified by asking the patient to cough and to perform a Valsalva maneuver while each vaginal wall is individually exposed.

To obtain baseline characteristics of both patients groups all patients are asked to fill in standardized questionnaires at inclusion. These questionnaires are validated quality of life questionnaires (RAND 36, Euroqol 5D, Urogenital Distress Inventory, Defecatory Distress Inventory, Incontinence Impact questionnaire) and two questionnaires regarding sexual functioning (Pelvic Organ Prolapse/Urinary Incontinence Sexual Questionnaire and selected items from the “Vragenlijst Seksuele Disfuncties”) [21–29]. Preoperative urodynamic evaluation is only performed in women with bladder dysfunction.

During hospitalization and in the first 6 weeks after surgery patients are asked to keep a diary which contains the following items: postoperative pain measured by Visual Analogue Score (VAS), used pain medication and the RI-10 recovery questionnaire. The RI-10 recovery questionnaire is a validated quality of life questionnaire measuring subjective postoperative recovery [30]. To prevent a recall bias as much as possible, patients will be phoned two and four weeks after surgery as a reminder to fill in the diary. After surgery, patients will visit the hospital at 6 weeks (routine post-operative consultation), 6 months, 12 months and yearly thereafter. The total duration of the follow-up is 5 years. Each check-up includes a standardized written questionnaire regarding quality of life and sexual functioning (similar to the questionnaires at baseline) and a clinical examination (including POP-Q).

The validated questionnaires will be administered by the participating hospitals (baseline and 6 weeks postoperative) and by the coordinating hospital (6 months postoperative and yearly thereafter).

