### Statistical analysis

#### Sample size and power calculations

Sample size calculation was performed using Sample Power 2.0 (SPSS inc. Chicago, IL, USA). The aim of the study is to clarify whether laparoscopic sacrohysteropexy and vaginal sacrospinous hysteropexy do not differ significantly in surgical success rates of the apical compartment. We aim to demonstrate non-inferiority of the laparoscopic sacrohysteropexy at both 1 and 5 year (i.e. two tests on the primary endpoint will be performed). Two groups of 55 patients will be included to yield a 80% power for a non-inferiority margin of 10% assuming a recurrence rate of prolapse at the apical compartment of 3%. Taking into account 10% attrition, a number of 62 patients will be included in each study arm. This dropout can be expected when patients, after randomization, are unhappy with their allocated treatment and choose to end their participation in the study or due to incomplete or lost data. A total number of 124 women will be included in this study.

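### The independent physician who examines the women at 1 and 5 years is not said to be kept unaware of the allocation, so the anatomical part of the primary endpoint is open to observer bias of unknown size and direction

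*Protocol article*

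**What the plan says.** The Study design section calls LAVA a "prospective, randomized controlled non-blinded clinical trial" and gives the reason that "it is impossible to blind the participating patients and the health care workers for the surgical procedure" to which the woman is allocated. It then sets one safeguard against this: "follow-up at six months, one and five years will be done by a physician not involved in the surgery". The article says nothing further about concealing the arm from the person who examines the woman.

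The primary outcome is a composite, assessed at 1 and 5 years. Under Primary and secondary outcomes: "Success is defined as position of the cervix at or above the mid-vagina (C < -TVL/2), no symptoms" of bulging or protrusion on the questionnaire, and no reoperation or pessary for recurrent apical prolapse. The combining rule is "Failure in one of these areas will constitute a failure".

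Under Data collection, the preoperative staging examination is described in detail: "Maximum prolapse is demonstrated and identified by asking the patient to cough and to perform a Valsalva maneuver". For the follow-up visits the section says only that the clinical examination includes POP-Q.

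**The concern.** Independence from the surgery and ignorance of the allocation are different safeguards. The first removes the motive of a surgeon who judges her or his own work. Only the second prevents expectations about the two operations from entering the reading. The plan already places a physician from outside the operation at both primary time points, and such a person could in principle be kept unaware of the arm. As written, nothing requires it.

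The cervix criterion is a cut-off on a measurement made by that examiner, and failing it alone makes the woman a failure. A reading close to -TVL/2 can therefore change her primary outcome. With very few failures expected, a handful of such readings could decide whether non-inferiority is concluded.

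**Working it through.** **Inputs (Sample size and power calculations; Data analysis).** 55 evaluable women per arm, 62 after 10% attrition; 3% recurrence, taken as equal in both arms (Abstract); margin 10 points; 80% power; decision by the 95% CI.

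**The plan's own figure.** The unpooled normal approximation is n = 2 × 0.03 × 0.97 × (z₁₋α + z₀.₈)² / 0.10².
- One-sided 0.0125 (0.025 halved for the two tests): 55.3, which is the stated 55 to within one patient.
- One-sided 0.05 with continuity correction: 54.1, so 55.
- One-sided 0.025, as the 95% CI implies: 45.7, so 46.
- Attrition: 55 / 0.90 = 61.1, so 62, as stated.

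Which α was used does not affect this point.

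**Expected failures.** 55 × 0.03 = 1.65 per arm, so about 2.

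**How many changed classifications reverse the conclusion.** Let p_L and p_V be the laparoscopic and vaginal failure proportions. The Wald upper limit is p_L − p_V + 1.96 × √[p_L(1−p_L)/55 + p_V(1−p_V)/55]. The Newcombe upper limit is p_L − p_V + √[(u_L − p_L)² + (p_V − l_V)²], where u_L is the upper Wilson limit of the laparoscopic arm and l_V the lower Wilson limit of the vaginal arm.

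For 2 v 2: p = 2/55 = 0.0364 in both arms, with Wilson limits 0.0100 and 0.1232.
- Wald: 0 + 1.96 × 0.0357 = 0.070.
- Newcombe: √(0.0868² + 0.0264²) = 0.091.

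| Failures, laparoscopic v vaginal (55 per arm) | Wald upper limit | Newcombe upper limit |
|---|---|---|
| 2 v 2 | 7.0 points | 9.1 points |
| 3 v 2 | 9.6 | 11.6 |
| 4 v 2 | 12.1 | 14.0 |

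With 2 vaginal failures, non-inferiority therefore allows at most 3 laparoscopic failures (Wald) or 2 (Newcombe; the Farrington-Manning score test agrees). The same maxima apply at 62 per arm.

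**What an assumed misclassification would do.** These are exact binomial calculations at 55 per arm. An average of k misclassified women is represented by moving the laparoscopic failure rate by k/55. The values k = 1 and 2 are assumptions for illustration.

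| Scenario | k | Chance of concluding non-inferiority, Wald | Newcombe |
|---|---|---|---|
| True rates 3% v 3%; k successes read as laparoscopic failures | 0 | 0.849 | 0.651 |
| | 1 | 0.626 | 0.397 |
| | 2 | 0.408 | 0.220 |
| True rates 13% v 3% (at the margin); k laparoscopic failures read as successes | 0 | 0.048 | 0.018 |
| | 1 | 0.096 | 0.039 |
| | 2 | 0.181 | 0.080 |

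An average of one misclassified woman roughly doubles the false-positive rate in one direction. In the other it removes more than 20 percentage points of power.

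**The case against.** The strongest reply is that the article discloses an open design, gives a reason and provides a partial safeguard. The reason names health care workers in general, which can include the follow-up physician, so it cannot be read as confined to the operating team. An article also condenses its full protocol, and details such as forms, file access and draping commonly sit elsewhere. This stands in part: there is no contradiction here, and the absence of examiner procedures is not in itself a fault. But the Study design section is not silent on blinding. It declares the trial non-blinded and names its safeguard, and that safeguard does not conceal the arm.

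Several stronger readings are tempting, and the documents do not support them:
- **That the examiner is known to be unmasked.** This is an inference from the open-label statement and from the lack of any masking provision. No sentence says it.
- **That the counts measure observer bias.** They would be the same with a perfectly masked examiner, because they follow from the low expected failure rate. How many readings lie near -TVL/2, and how far expectation moves them, is not given.
- **That the bias must favour non-inferiority.** Missed laparoscopic failures would help the claim, but false ones would harm it. Over-calling failures equally in both arms also harms it: 3 v 3 gives a Newcombe limit of 10.06 points and 5 v 5 a Wald limit of 10.74, both beyond the margin.
- **That point C is read under Valsalva at 1 and 5 years.** The maneuver is described only for the preoperative examination, so its use at follow-up is plausible but not stated.
- **That cervix readings alone decide the trial.** A woman whose C is read as satisfactory still fails if she reports bulging or has had a reoperation or pessary for recurrent apical prolapse. Symptom reports come from women who know their operation.

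Masking is also imperfect. Port scars, or the scar of the posterior vaginal wall incision, may reveal the arm.

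**Conclusion.** The point holds as a design weakness that should be corrected. Followed as written, the plan lets the anatomical component at 1 and 5 years be read with knowledge of the allocation by a physician who could be kept unaware of it.

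The size and direction of any bias are unknown. What can be stated is the fragility: from 2 v 2 at 55 per arm, one changed classification (score-type interval) or two (Wald) reverse the non-inferiority conclusion. This rests on the protocol's 3% failure rate. If observed failures are well above that, one or two readings matter less.

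**What to change.** In the Study design section, state that the independent examiner at 1 and 5 years is kept unaware of the allocation as far as possible, and how:
- POP-Q is recorded before the file or operative notes are opened.
- The allocation does not appear on the examination form.
- The woman's abdomen is covered.
- The woman is asked not to mention which operation she had.
- The examiner's guess of the arm is recorded, so that failed masking can be measured and reported.

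The cost is an instruction to examiners and a form change. No extra staff or visits are needed and the sample size is unchanged. It has to be in place before the first 1-year examinations, since readings cannot be masked afterwards. Masking will sometimes fail because of port scars or the posterior wall scar, and it does nothing about bulge symptoms reported by unblinded women. The trial report should state both limits.

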**Figure 1 Fig1:**
[figure not shown]
**Study design.**

### Primary and secondary outcomes

Surgical success of the middle compartment at 1 and 5 years follow-up in both study groups will be considered as the primary outcome. Success is defined as position of the cervix at or above the mid-vagina (C < -TVL/2), no symptoms (defined as no symptoms of vaginal bulging and protrusion on the validated questionnaire) and no reoperation or pessary use for recurrent apical prolapse [20]. Failure in one of these areas will constitute a failure. Secondary outcomes of this study include prolapse of the anterior and posterior compartment, subjective outcome and improvement in general and disease-specific quality of life, complications, hospital stay, postoperative recovery, sexual functioning, cost-effectiveness and uterine issues (e.g. abnormal bleeding, cervical dysplasia) and the need for subsequent hysterectomy.

### Study population and recruitment

All women seeking treatment for symptomatic pelvic organ prolapse with uterine descent POP-Q stage 2 or higher are eligible for inclusion in the LAVA trial. A total of 124 women will participate in this trial. Patients with co-existing anterior/posterior defects or concomitant incontinence surgery can be included.

Women with previous pelvic floor or prolapse surgery, known malignancy of the cervix or cervical dysplasia, language barriers, a wish to preserve fertility, presence of immunological or hematological disorders interfering with recovery after surgery, contraindications for laparoscopic surgery (e.g. ileus, risk of severe adhesions), abnormal ultrasound findings of uterus or ovaries which cause symptoms and/or require treatment, abnormal uterine bleeding that requires surgical treatment, postmenopausal bleeding in the past year and women who are unwilling to return for follow-up are excluded from this study. Inclusion of women with cervical elongation will be left to the discretion of the enrolling surgeon. In case the surgeon believes that surgical shortening of the cervix or even vaginal hysterectomy is more appropriate because of a distinct elongation the patient should not be enrolled. Assessment for eligibility is performed by a gynecologist of the participating hospital. Patients eligible for this study are counseled about the long duration of follow-up required for this study. Subsequently, written patient information is provided, which contains information on the objectives, design, methods, possible advantages and disadvantages of the study treatments, and information that non-co-operation with the study or withdrawal will not have consequences for their treatment. An interval of at least one week between the primary visit and the next appointment allows sufficient time for women to think about participation. Before randomization, written informed consent is obtained.

